
### Study Procedure

The study consists of two phases: (1) planning intervention strategies for the intervention group, including the development of the educational content to be covered during the antenatal and postnatal periods and the development of the mHealth app, audio, and videos related to postnatal care, and (2) implementation of the SEPP and investigating its effectiveness on parental outcomes.

This study has been approved by the ethics board, and recruitment at the antenatal clinics has started at the study venue. The principle investigator and her team will inform nurse managers and clinicians at the antenatal clinics before a RA (RA1) commences the process of recruitment. Before contacting potential participants, the attending nurses and/or clinicians will be approached to assess each couple’s physical and psychological well-being before inviting them to participate in the research study. The referred couples will once again be assessed using the inclusion and exclusion criteria. There will be no undue influence or coercion used to recruit couples into the study. Each couple will be given details of the purpose of the study and ample time to ask questions and to consider before deciding to participate. It will be strongly emphasized that their participation is solely voluntary and that they may choose not to participate without any harm or compromise in the care they receive. Verbal and written consent will be obtained from the couple, both mother and father, thereafter. Both first-time and experienced mothers, regardless of their parity, who meet the inclusion criteria, along with their partners, will be recruited. RA1 will visit the antenatal clinics regularly to recruit participants according to the inclusion and exclusion criteria and will be responsible for randomizing the participants.

Once consent has been taken, demographic and baseline data of the participants will be obtained, and randomization will take place. In addition, recruited couples will be asked for their contact details so that they can be contacted for subsequent follow-ups. RA1 will keep in constant contact with the participants to ensure the birth of the newborn. For participants in the intervention group, telephone-based antenatal education session will be delivered by RA1 at the participants’ convenience at a prearranged timeslot.

After childbirth, all couples will be reapproached in the postnatal wards by the RA before their day of discharge post childbirth. Before making contact in the postnatal wards, the nurse-in-charge will be approached by RA1 to ensure the physical and emotional well-being of the participants. For participants in the intervention group, the postnatal education session will be delivered by RA1 in the postnatal wards on the day of discharge from the hospital. RA1 will assist parents in downloading the mHealth app and demonstrate the functions of the app before discharge. Participants will also be given individual usernames and passwords for access to the mHealth app. Access to the app will expire automatically in 4 weeks. RA1 will be responsible for answering the queries in the discussion forum and to monitor and correct any inappropriate content shared among parents.

### Data Collection

A single-blind technique will be adopted, in which the RA (RA2) responsible for the collection of data post intervention or post discharge will not be aware of the treatment allocation, which will be conducted by another RA (RA1). RA2 will be responsible for the collection of all interim and postintervention data, including the process evaluation interviews. Outcome measures will take place at the following time points for all parents: (1) during pregnancy, before randomization (baseline); (2) after childbirth, before hospital discharge (interim data); (3) post intervention for the SEPP intervention group and at the end of week 4 post childbirth for the control group (posttest 1); and (4) 2 months after the SEPP for the intervention group and 3 months post childbirth for the control group (posttest 2). The period when parents are prone to facing various challenges is at 1 month post birth. Hence, the rationale for collecting posttest 1 data during that time. At 3 months post birth is when some working mothers return to work, signifying a change in environment relating to the rational for collecting posttest 2 data. Before contacting parents for the posttest data, a message will be sent to ensure parents’ availability. In the process of data collection, if either parent feels tired, RA2 will respect the parents’ decision to continue or terminate the data collection to ensure parents’ comfort. The consolidated standards of the reporting trial flowchart for this study is presented in Figure 7 [56].

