### Sample Size Determination

On the basis of previous studies, psychosocial and educational interventions in the perinatal period generally produce a medium size effect on outcome variables [27,28]. Hence, the SEPP intervention can also be assumed to have a medium effect size on outcome variables. A repeated measure analysis of covariance (ANCOVA) will be used to test for differences between two groups (intervention and control) and within four separate time points and for interaction (group x time) effects. The required sample size for the detection of a medium effect size of 0.3 (analysis of variance [ANOVA] *F* value) at a power of 80% and a significance level of 5% (two-sided) is 45 in each group [40]. Considering a 30.0% (30/100) attrition rate based on previous studies [27,29], a minimum of 118 participants (45x2 + 45x2x30%=90 + 28=118), with 59 in each group, is needed. A purposive sample of approximately 16 participants will be needed for the process evaluation. Parents with differing mean parenting efficacy (primary outcome) scores from both the intervention and control groups (8 from each group) will be selected to participate in the face-to-face interviews, until data saturation is attained.

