### Outcome Measures and Instruments

Patients’ demographic data (eg, age, gender, ethnicity, and education) will be collected. In addition, the following instruments will be used to measure parental outcomes:

Parenting Efficacy Scale (PES): This 10-item PES scale [41] is used to measure parental beliefs on self-efficacy. Nine of the items refer to specific behaviors related to infant care (eg, feeding and bathing), and the last item is a global evaluation of parenting ability. The total score of PES ranges from 10 to 40, with higher scores indicating higher PSE. The Cronbach alpha value of the PES was .74 in the previous study [42].Parent- Infant Bonding Questionnaire (PIBQ): This is an 8-item, 4-point Likert scale used to measure the parental bonding of both parents [43]. The total scores range from 0 to 24, with higher scores suggesting ineffective bonding between mother and infant and vice versa. The cut-off score indicating poor bonding between parent and infant is indicated at 2 [44]. The Cronbach alpha for this questionnaire was .7 in the previous study [45].Edinburgh Postnatal Depression Scale (EPDS): This is a 10-item scale widely used to measure parents’ postnatal depression [24,29,46-48]. The total score of the EPDS ranges from 0 to 30. The recommended cut-off score of 12 or 13 is used for screening probable cases of postnatal depression. The sensitivity of the EPDS ranges from 68% to 80%, with 77% specificity and a Cronbach alpha of .88 [49].State Trait Anxiety Inventory (STAI): This is a 40-item 4-point Likert scale used to measure parental anxiety level. The total score for the STAI ranges from 40 to 160, with higher scores indicating greater levels of parental anxiety. The scale has been tested widely in various studies [50-53]. The Cronbach alpha for the STAI was .8 in a previous local study [52].Perceived Social Support for Parenting (PSSP): This is a 4-item scale [42] used to measure the social support parents receive from their partners or others. The score of the 5-point Likert scale ranges from 0 to 20 for the support received from partners or others. The instrument showed high internal consistency and had a Cronbach alpha of .81 in a previous study [42].What Being the Parent of a Baby is Like (WBPL): The evaluation subscale of the WBPL will be used to measure parenting satisfaction [54]. It consists of 11 items, and each item is a 10-point semantic differential scale ranging from 0 (none of the phenomenon) to 9 (a great deal of the phenomenon). In previous studies, the Cronbach Alpha ranged from .91 to .92 [54,55].Health care utilization and program-related expenses sheet: This sheet will be used to capture all direct health systems cost related to health care services utilized antenatally and postnatally because of maternal or infant related health issues such as hospital admissions and outpatient contacts, health professional’s time, program-related time, and during pregnancy, for the first and 3rd month after delivery. The study will take an *all-payer* health system perspective in which it will attempt to capture all resources that are used by the participants, regardless of who the payer is (ie, government or consumer), including the program cost. The measurement period begins from entry into the program until 3 months post birth.A semistructured interview guide will be used for the process evaluation. Individual face-to-face interviews will be conducted immediately after the intervention (1 month post birth) to identify strengths and weaknesses and to comment on the content, activities, effectiveness, and delivery methods of the SEPP for participants in the intervention. Parents in the control group will be asked to comment on the current routine perinatal care provided by the hospital. All interviews will be audiorecorded.

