### Process Evaluation

Process evaluation will be conducted with the main objective of obtaining parents’ opinions and comments of the SEPP intervention. Purposive sampling of parents will be done based on the parenting self-efficacy scores of parents immediately after the end of the intervention (at 1 month post childbirth). This will be done through a semistructured face-to-face interview. Each interview will take approximately 20 to 30 min and will be audiorecorded. Parents will not be included for interview if they refused to be audiorecorded. The recruitment for process evaluation will continue and will only be terminated once the proposed number of interviews is reached or when data saturation is achieved. The semistructured interview guide has been reviewed and approved by the ethics board.

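### RA2 holds arm-specific interviews with about 16 parents at 1 month, so posttest 2 for those parents cannot be assessor-blind as the protocol claims

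*Protocol article*

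**What the plan says.** All references are to the protocol article.

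- **Blinding claim (Data Collection).** The trial is single-blind in that RA2, who gathers the data after the intervention or after discharge, "will not be aware of the treatment allocation, which will be conducted by another RA (RA1".
- **RA2's duties (Data Collection, next sentence).** "RA2 will be responsible for the collection of all interim and postintervention data, including the process evaluation interviews". The last assessment, posttest 2, falls 2 months after the SEPP ends in the intervention arm and 3 months after birth in the control arm.
- **Timing of the interviews.** Outcome Measures and Instruments: "Individual face-to-face interviews will be conducted immediately after the intervention (1 month post birth". Process Evaluation agrees: "immediately after the end of the intervention (at 1 month post childbirth".
- **Content of the interviews (Outcome Measures and Instruments).** Intervention parents comment on matters that include the "delivery methods of the SEPP for participants in the intervention". For the other arm, "Parents in the control group will be asked to comment on the current routine perinatal care provided by the hospital".
- **Number (Sample Size Determination).** "A purposive sample of approximately 16 participants will be needed for the process evaluation", and parents "from both the intervention and control groups (8 from each group) will be selected".
- **Transcription (Data Analysis).** RA2 transcribes the recordings while data collection is still under way.

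**The concern.** RA2 has to know a parent's arm to put the right questions, and the answers would disclose it in any case. Two months later the same RA2 collects that parent's final outcomes. For these parents the stated blinding and the stated duties cannot both be true.

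RA2 is the only person whom the article describes as blinded. Parents know what they received. RA1 randomizes, delivers the sessions and answers the forum. If the plan runs as written, the trial would report assessor-blinded 3-month outcomes, including the primary outcome (PES), although its own procedures remove that property for a known subset. An assessor who knows the arm could affect self-reported scores through how the questionnaire is administered, prompted and followed up.

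**Working it through.** The plan gives no figure on this point to reproduce. The check is a comparison of sections, followed by a count of the parents affected.

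**Order of events for an interviewed parent**

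| Time | Event | Does RA2 know the arm through the interview? |
|---|---|---|
| Pregnancy, before randomization | Baseline | No |
| After birth, before discharge | Interim data | No |
| About 1 month | Posttest 1 | Normally no |
| About 1 month | Process interview, then transcription | Yes, from here on |
| About 3 months | Posttest 2 | Yes |

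The entry for posttest 1 is an inference. Process Evaluation selects interviewees on their self-efficacy scores at the end of the intervention, so those scores should exist before the interview. No section moves the interviews to a later date or gives the interviewees' posttest 2 to another assessor.

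**Share of parents affected**

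Inputs: 16 interviewees, 8 per arm, 118 participants with 59 per group, and 30% attrition (all Sample Size Determination); 118 couples (Results).

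- 118 taken as parents: 16/118 = 13.6%. Per arm, 8/59 = 13.6%.
- 118 taken as couples: 2 × 118 = 236 parents, and 16/236 = 6.8%.
- 118 parents with 30% lost: 118 × 0.70 = 82.6 remain. If every interviewee is retained (assumption), 16/82.6 = 19.4%.
- Partners included: the Design section assigns couples to groups, so one parent's interview may also disclose the partner's arm. If all 16 come from different couples (assumption), up to 32 parents are affected: 32/118 = 27.1%, or 32/236 = 13.6%.

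The number 16 is itself approximate. Process Evaluation lets interviewing end sooner if saturation is reached.

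**The case against.** The strongest reply is that little depends on RA2. The outcomes are fixed-item self-report scales, and parents know their arm. The larger reporting bias therefore lies with the parents, and no assessor blinding removes it. This stands, and it is why the expected effect is modest. It does not reconcile the two statements in Data Collection.

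A reader might infer more than the document supports in four ways.

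- **That blinding fails for the whole trial.** It certainly fails only for the interviewees at posttest 2, and possibly for their partners. RA2 might learn what the SEPP contains and recognise it when other parents mention it, but no section says so. A parent could also reveal the arm at any contact, whoever holds the interviews.
- **That a size of bias can be stated.** Suppose RA2's knowledge shifted the interviewees' scores by a in the intervention arm and by b in the control arm. The difference in means would move by (8/59)(a − b) = 0.136(a − b) with 59 per arm. The document gives neither a nor b. Both arms are interviewed in equal numbers, so equal shifts cancel. Any single figure would rest on an assumed shift in one arm only.
- **That choosing interviewees by PES score makes the bias worse.** Sample Size Determination asks for differing scores in both groups and states no direction. The choice does not alter the data analysed.
- **That RA2 picks the interviewees.** Neither Sample Size Determination nor Process Evaluation says who does.

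**Conclusion.** The point holds in a limited form. The single-blind statement is wrong for posttest 2 in about 16 parents: 13.6% of 118 parents, or 6.8% if the target is 118 couples. It may also be wrong for their partners. Baseline and interim data are clear of this route, and posttest 1 normally is too.

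The conclusion rests on three things that the article states: the interviews take place at 1 month, their content differs by arm, and RA2 both conducts them and collects posttest 2. The consequence for the treatment estimate is likely to be modest and cannot be quantified from the document. The plan should still be changed, because the claim is contradicted by the sentence that follows it and the repair is small.

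**What to change.** Either of two changes restores the claim.

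1. Have one of the two investigators already assigned to the qualitative analysis, or another team member who collects no outcomes, conduct and transcribe the interviews. RA2 should have no access to recordings or transcripts while outcome collection continues. At 20 to 30 minutes each, 16 interviews take 16 × 20 = 320 to 16 × 30 = 480 minutes, about 5 to 8 hours, plus transcription. The cost is that time, and parents may be less frank with an investigator.
2. Keep RA2 as interviewer, but hold each interview after that parent's posttest 2, and after the partner's as well if couples share an allocation. RA2's time is unchanged. The cost is a recall gap of about two months and a departure from the stated timing at the end of the intervention.

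If neither is done, and for any interviews already held, state that posttest 2 for interviewees is not assessor-blind, and report a sensitivity analysis of the 3-month outcomes without them. That analysis loses about 8 parents per arm, so it serves as a check on the main result and should not replace it.

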### Process Evaluation

Process evaluation will be conducted with the main objective of obtaining parents’ opinions and comments of the SEPP intervention. Purposive sampling of parents will be done based on the parenting self-efficacy scores of parents immediately after the end of the intervention (at 1 month post childbirth). This will be done through a semistructured face-to-face interview. Each interview will take approximately 20 to 30 min and will be audiorecorded. Parents will not be included for interview if they refused to be audiorecorded. The recruitment for process evaluation will continue and will only be terminated once the proposed number of interviews is reached or when data saturation is achieved. The semistructured interview guide has been reviewed and approved by the ethics board.

### Data Analysis

All quantitative data will be analyzed using Statistical Package for the Social Sciences (SPSS) version 24.0 (IBM Corp). Missing data will be replaced (assuming 10%) for intention-to-treat (ITT) analysis. Both ITT analysis and per-protocol analysis will be conducted to compare any differences between groups. Descriptive statistics such as mean, standard deviation, and range for continuous dates, frequencies, and percentages will be used for nominal and ordinal data. Cronbach alpha will be used to test the internal consistencies of the questionnaires. Inferential statistics such as the independent *t* test or ANOVA will be used to compare differences of outcomes between or among demographic subgroups. Presuming that outcomes variables are normally distributed, parametric tests will be used. Repeated measures ANCOVA adjusted for confounding variables will be used to test the effect of intervention on outcome variables across four time points. Univariate ANCOVA will be used to test the differences in outcome variables between two groups at the interim and two posttests data separately.

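### The intention-to-treat analysis assumes 10% missing data while the sample size assumes 30% attrition; the two are not reconciled, and replacing values is a weak basis for the main test.

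*Protocol article*

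**What the plan says.** The protocol article, Data Analysis section, says: "Missing data will be replaced (assuming 10%) for intention-to-treat (ITT) analysis". It continues: "Both ITT analysis and per-protocol analysis will be conducted to compare any differences between groups". The main test is a repeated measures ANCOVA adjusted for confounders, which "will be used to test the effect of intervention on outcome variables across four time points". Separate univariate ANCOVAs are planned at the interim and the two posttest points.

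The Sample Size Determination section uses a different figure: "Considering a 30.0% (30/100) attrition rate based on previous studies". It adds that allowance to 45 per group and reaches 118 participants, 59 per group.

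The article does not link the two percentages, define what the 10% counts, or name a replacement method.

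**The concern.** The 10% is attached to the intention-to-treat analysis, and what threatens that analysis is the loss of randomised participants. Elsewhere the article expects three times that loss. Some loss is also built into the design. The Participants section says couples recruited antenatally may be excluded if complications arise in pregnancy or delivery, and the Data Collection section lets a tired parent end a session.

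The figure matters because of the chosen test. Repeated measures ANCOVA in its standard form uses only participants with every time point complete, so here the filled-in values are what create the intention-to-treat set. The larger the missing share, the more the result depends on the replacement rule. If values filled in once are then counted as data, the standard error can be too small and the type I error too high, or the group difference can be pulled towards zero.

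**Working it through.** **The plan's own figures**

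- Effect size: "detection of a medium effect size of 0.3", read as Cohen's f, so d = 2 × 0.3 = 0.6 for two groups. Power is 80% and alpha 5% two-sided.
- Exact noncentral F for two groups: 44 per group gives 79.5% power and 45 gives 80.4%. The stated 45 per group is reproduced.
- Attrition: 90 × 0.30 = 27, which the article prints as 28, and 90 + 28 = 118. The allowance as a share of those recruited is 28/118 = 23.7%.

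**The two assumptions side by side, for 118 participants**

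- Data Analysis: 10% × 118 = 11.8, about 12.
- Sample Size Determination: 30% × 118 = 35.4, about 35, or 28 by the article's own sum.

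**What the gap would mean under single replacement**

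The methods below are assumptions, because the article names none. The setting is a two-group comparison at one time point, n per arm, outcome variance σ², a fraction m missing completely at random in each arm, participants treated as independent, and filled-in values analysed as observed.

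1. *Arm-mean replacement.* The arm mean is still the observed mean, with true variance σ²/[n(1−m)]. The filled-in values add nothing to the sum of squares, so the model reports about (1−m)σ²/n. The ratio of reported to true standard error is 1−m.
2. *One random draw per gap.* The true variance of the arm mean is (σ²/n)[1/(1−m) + m] and the model reports σ²/n. The ratio is 1/√[1/(1−m) + m].
3. *Overall-mean replacement.* Both arms receive the same value, so the estimated difference is multiplied by 1−m. Under the null the reported and true standard errors shrink together, so the ratio is about 1.

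Type I error = 2 × [1 − Φ(1.96 × ratio)].

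| m | Arm mean: ratio, type I | Random draw: ratio, type I | Overall mean: type I, difference kept |
|---|---|---|---|
| 10% | 0.90, 7.8% | 0.91, 7.5% | near 5%, 90% |
| 23.7% | 0.76, 13.5% | 0.80, 11.5% | near 5%, 76% |
| 30% | 0.70, 17.0% | 0.76, 13.6% | near 5%, 70% |

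A simulation under the null (40,000 runs, 59 per arm) agrees. With 6 of 59 missing per arm it gave 7.8%, 7.4% and 4.9% for the three methods in table order. With 14 of 59 it gave 13.6%, 11.6% and 5.0%. With 18 of 59 it gave 17.5%, 13.6% and 4.9%. The arm-mean result of 17.5% is slightly above the formula because 18/59 is 30.5%.

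**The case against.** The strongest reply is that the two percentages may describe different things. The 30% is an allowance for setting recruitment and may be deliberately cautious. The 10% could be an expected rate, or could refer to unanswered items or visits among parents who stay in the study. This stands to the extent that a reader might infer that the two figures cannot both be true, and the text does not go that far. It shows only that they differ and are not explained. If the 10% does mean item non-response, however, the sentence leaves the expected loss of participants unaddressed, so it needs amending on either reading.

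A second reply is that the harm is hypothetical. A reader might infer that the intention-to-treat analysis will treat filled-in values as observed and understate its standard errors. The article does not say so. Multiple imputation also replaces missing values and, properly pooled, does not have this fault. A journal article may leave the method to a fuller document, so the unnamed method is not itself a fault. This stands, and the error rates above are conditional.

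Three further limits also stand. Missingness of a third is not supported: the article gives 30%, or 23.7% by its own sum. Carrying the antenatal score forward is mentioned nowhere and should not be attributed to the plan. The calculation concerns one time point, whereas the main test spans four. Baseline precedes randomisation and the interim measure precedes discharge, so losses would accumulate, and 30% would not plausibly apply at every point.

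**Conclusion.** The point holds as an unreconciled pair of planning figures, 10% against 30% (23.7% by the article's own sum), joined to an analysis that relies on replacement to form its intention-to-treat set. That much rests on the text alone.

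The statistical consequence depends on a method the article does not give. If single replacement analysed as observed data is meant, type I error at one time point with 30% missing completely at random lies between near 5% and about 17%. At 10% missing it lies between about 5% and 7.8%. The lower end is not harmless, because overall-mean replacement would remove 30% of the estimated difference at 30% missing. Under pooled multiple imputation the standard-error problem would not arise. Inflated error is therefore a risk that the wording leaves open, and it grows with the missing share. It is not an established defect.

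**What to change.** In the Data Analysis section, drop the sentence on replacing missing data and the repeated measures ANCOVA as the intention-to-treat analysis. Specify instead a likelihood-based linear mixed model on all observed post-birth scores (interim, posttest 1 and posttest 2) of all randomised parents, adjusted for the baseline score. This keeps every parent with at least one post-birth score and needs no filled-in values.

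The model relies on drop-out being explained by the observed data. Add multiple imputation with a shift applied to drop-outs as a sensitivity analysis, so that the result is also tested where that assumption fails.

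Reconcile the expected missingness with the Sample Size Determination section, or state that the 10% refers only to item non-response. The article does not establish which figure is the better forecast, so the investigators should give the basis for the one they keep.

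The cost is revised wording and a little more analysis work. The mixed model can be run in the software already named. The Results section reports recruitment as still under way, and the change needs no new participants, visits or data.

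### The repeated-measures ANCOVA counts the pre-randomisation score as one of its four outcome time points, which dilutes the group main effect; that score belongs on the covariate side

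*Protocol article*

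**What the plan says.** Data Collection lists four measurement times. The first is "during pregnancy, before randomization (baseline"); the others are before hospital discharge after the birth (interim), about 1 month (posttest 1) and about 3 months (posttest 2).

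Data Analysis puts all of them in one model: "Repeated measures ANCOVA adjusted for confounding variables will be used to test the effect of intervention on outcome variables across four time points". Sample Size Determination says that this model tests the difference between the two groups, and also differences "within four separate time points and for interaction (group x time) effects". The covariates are described only as confounding variables; the baseline score is not named among them.

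Data Analysis then adds: "Univariate ANCOVA will be used to test the differences in outcome variables between two groups at the interim and two posttests data separately". Both intention-to-treat (ITT) and per-protocol analyses are planned.

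The trial is sized for "detection of a medium effect size of 0.3" "at a power of 80% and a significance level of 5% (two-sided) is 45 in each group". Parenting self-efficacy, measured by the PES, is the primary outcome under Aims. No visit, model term or analysis set is named as deciding it.

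**The concern.** Randomisation cannot change a score recorded before it, so the expected group difference at the first time point is zero. If that score is an outcome level, the group main effect averages a zero with the later differences, and its power falls. The same score used as a covariate would remove variance and raise power. The plan thus spends its most useful covariate as an outcome level that carries no information on the treatment effect.

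The sample size takes no account of this, so a true benefit could be missed on the group term. A secondary matter is that several tests of the primary outcome stand side by side, and nothing in the article says which one decides.

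**Working it through.** **Inputs from the document.** Effect size f = 0.3, two-sided 5%, 80% power, 45 per group before attrition (Sample Size Determination); four visits, the first before randomisation (Data Collection).

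**Assumptions, not in the document.** SD 1 at each visit; the same correlation r between any two visits, taken as 0.3, 0.5 and 0.7; an effect of 0.6 SD at both posttests; an interim effect of either 0.6 SD (full) or 0.15 SD (small). All power figures use 45 per group.

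**1. The plan's own figure.** With two equal groups, d = 2f = 0.6. A two-sample t test at 80% power needs 44.6, so 45 per group, and 45 gives 80.4%. The stated number therefore reproduces as a single two-group comparison, with no term for repeated visits.

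**2. What the four-visit group effect estimates.**
- Full interim effect: (0 + 0.6 + 0.6 + 0.6)/4 = 0.45 = 0.75d.
- Small interim effect: (0 + 0.15 + 0.6 + 0.6)/4 = 0.3375, or about 0.56d.

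**3. Power of that group effect.** The variance of a four-visit mean is (1 + 3r)/4: 0.475, 0.625 and 0.775, so SD 0.689, 0.791 and 0.880.

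| | r = 0.3 | r = 0.5 | r = 0.7 |
|---|---|---|---|
| Full interim: 0.45/SD | 0.653 | 0.569 | 0.511 |
| Power | 86.5% | 76.1% | 66.9% |
| Small interim: 0.3375/SD | 0.490 | 0.427 | 0.383 |
| Power | 63% | 52% | 44% |

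With a full interim effect, 80% power would need about 38, 50 and 62 per group.

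**4. The loss due to the baseline level alone.** With a full interim effect, dropping baseline and averaging the three post-birth visits without adjustment gives variance (1 + 2r)/3 and power 97.1%, 93.2% and 88.2%, against 86.5%, 76.1% and 66.9% above.

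**5. Baseline as covariate.** These figures ignore the one degree of freedom spent on the covariate.
- Mean of the two posttests: variance (1 + r)/2 − r² = 0.56, 0.50 and 0.36; standardised effect 0.80, 0.85 and 1.00; power about 96%, 98% and over 99%.
- One posttest: variance 1 − r² = 0.91, 0.75 and 0.51; power about 84%, 90% and 98%.

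**6. Group-by-time term.** This is an F test on 3 and 264 df with noncentrality (45/2) × S/(1 − r), where S is the sum of squared deviations of the four effects from their mean.
- Full interim: S = 0.45² + 3 × 0.15² = 0.27; noncentrality 8.7, 12.2 and 20.3; power about 69%, 84% and 97%.
- Small interim: S = 0.287; noncentrality 9.2, 12.9 and 21.5; power about 72%, 86% and 98%.

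**7. Number of tests.** Group, group-by-time and three visit-wise ANCOVAs make five tests of the primary outcome in one analysis set. These were simulated with no treatment effect (10,000 runs per correlation, visit-wise tests adjusted for baseline). Each test alone holds about 5%. At least one of the two model terms is significant in about 9.7% of trials, and at least one of the five in 17.9%, 17.7% and 17.6%. Five independent tests would give 1 − 0.95⁵ = 22.6%.

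**The case against.** **The size of the loss is assumed.** This stands. The article gives neither effects by visit nor correlations. With a full interim effect and r = 0.3, the four-visit group effect has 86.5%, above the 80.4% of the sized test and slightly above a single adjusted posttest (84%). A reader might infer that the trial loses most of its power; the document does not support that as a general statement. In every case examined, however, the baseline-adjusted mean of the two posttests does better.

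**The group-by-time term already asks the right question.** This stands in part. In a pretest and repeated-posttest design it tests whether the groups diverge, and baseline does not dilute it. But it spreads the question over 3 df, does not say where the groups differ, and falls below 80% at r = 0.3.

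**The visit-wise ANCOVAs already leave baseline out as an outcome.** This is true, and the wording does not rule out baseline as their covariate. They do not repair the four-visit model, which is the one the article says tests the intervention.

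**Test order is commonly left to an analysis plan.** This is fair, and is why the multiplicity point is secondary. A reader might infer a false-positive rate of 18%. That needs a rule that any of the five tests counts as success, which the text does not state; the visit-wise tests can be read as follow-up. Nor does including baseline raise the error rate of any single test. Running per-protocol as well doubles the count of tests but not the error rate, because the two sets overlap heavily.

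**Two further inferences go too far.** One is that the interim score always precedes app access. Both the interim data and the app set-up fall before discharge and no order is given; the interim visit also follows the antenatal session, so it is a legitimate post-randomisation outcome. The other is that the antenatal PES measures something different. The article says "Nine of the items refer to specific behaviors related to infant care (eg, feeding and bathing"), but the item wording is not shown.

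**Conclusion.** The point holds for the group main effect. The text makes a pre-randomisation score an outcome level, so this effect estimates 0.75d under a constant later effect and less if the interim effect is small. That follows from the stated design and needs no assumed correlation.

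The cost in power does depend on assumptions. Across the ranges used, the four-visit group effect has between 44% and 87%, against 96% or more for the baseline-adjusted mean of the two posttests. The planned 45 per group was not derived for the four-visit model. Validity is not at risk from the baseline level itself; what is lost is efficiency and a clear estimate.

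The missing decisive test is a lesser matter of clarification: about 10% error if either model term could count, and about 18% if any of the five tests could, neither rule being in the text. The change should be made, but the plan is not unsound without it.

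**What to change.** - Use the antenatal score as a covariate and keep only the post-birth scores as outcome levels.
- Name one baseline-adjusted PES contrast in the ITT set as the primary test. The mean of the two posttests is one candidate; one posttest chosen in advance is another. The article gives a rationale for both posttests, so the choice is the investigators', provided it is made before outcome data are compared by group.
- Label the interim, group-by-time, other visit-wise and per-protocol results supportive.
- State which comparison the 45 per group refers to.

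This changes analysis wording only: the antenatal score is already collected, and no participants or visits are added. The price is that a result seen only on another contrast, or only per-protocol, could not be claimed as primary.
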